#### **Treatment procedure**

The intervention protocol was based on a preliminary clinical trial, utilized an electroacupuncture instrument (Hwato, SDZ-II B, Suzhou, China) and special silica gel ear clips. Patients in both groups received electrical stimulation at the bilateral auricular cymba conchae(auricular point kidney, CO10) and cavum conchae(auricular point heart, CO15), where there is rich of vagus nerve distribution. Patients in taVNS group received stimulation parameters, including dilatational wave at 4/20Hz (4Hz for 5 seconds, 20Hz for 10 seconds, alternately), pulse width of 0.2ms±30%, and intensity adjusted to the patient's maximum tolerable level (0.8~1.5mA). The sham taVNS group received the same parameters with a current intensity of 0.1mA.

On the day of enrollment, each patient will be taught to use the instrument, informed of precautions, and ensure that each patient could treat himself at home. Patients in both groups start treatment on the day of randomization and bilateral auricles receive stimulation simultaneously for 30 min each time, twice a day, five consecutive days a week, for 8 weeks, followed by a 12-week observational period. Sleep treatment diary will be used to monitor the patient's treatment and sleep status.

Patients are encouraged to avoid using medications or other therapies for treatment of insomnia throughout the trial. In accordance with the Declaration of Helsinki, if patients have severe insomnia and affect their daily life, temporary use of sleeping pills is allowed (the frequency of continuous use of drugs is allowed to be less than 3 nights), and the name and dose of drugs are recorded in the sleep diary and informed to the responsible doctor. For those who were under anti-hyperlipidemic, antihypertensive and anti-diabetic treatment, they were allowed to continue their current medications throughout the study. Drug history of the participant will be systematically recorded in the case report form.

#### **Monitoring of treatment compliance**

Self-report daily diary will be used to monitor treatment compliance. The treatment diary will record the number of times and the length of the treatment each day. The compliance is calculated by taking the number of times the patient is actually treated divided by the number of times the patient should be treated and multiply by 100.

## Clinical and biochemical assessment

Efficacy: The efficacy of the taVNS for chronic insomnia disorder will be associated with the primary outcome and secondary outcome.

The primary outcome is PSQI. The primary endpoint is the mean changes from baseline through week 8 in PSQI scores.

Secondary outcomes include the mean changes in PSQI scores at 4, 20 weeks, the response rate at 4, 8 and 20 weeks, as well as the changes in seven components of PSQI, Insomnia Severity Index (ISI), Hamilton Depression Scale (HAM-D-17), Hamilton Anxiety Scale (HAM-A-14), Epworth Sleepiness Scale (ESS), and Flinders Fatigue Scale (FFS) from baseline to 4, 8 and 20 weeks. Adherence is monitored through the sleep treatment diary. Additionally, adverse reactions are recorded. The response rate was defined as the percentage of patients with a reduction of  $\geq 50\%$  from baseline in the PSQI score after treatment.

Other clinical assessments will be conducted at baseline, 4 weeks, 8 weeks and 20 weeks. Blood pressure will be measured by clinical sphygmomanometer with the cuff placed around the upper arm. It will be measured in the morning at resting state after sitting quietly for at least 15 minutes. The measurement will be conducted in the same arm and no talking will be allowed during the measurement.

Safety: The safety of the taVNS will be associated with adverse events (AEs) reported by participants and recorded by physician. The incidence, intensity, subjective feeling of the relationship with the treatment, and management of the event will be recorded. Safety assessment will be conducted at 4 weeks, and 8 weeks. The reasons for withdrawal will be recorded when a subject withdraws before completing the study. Serious AEs are defined as any undesirable experience that is fatal, is life-threatening, requires initial or prolonged in-patient hospitalization, or causes persistent or significant disability or permanent damage.

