## PLAN OF INVESTIGATION

**Outline:** A randomized controlled trial is designed to test the clinical efficacy of taVNS in the treatment of insomnia for 8 weeks and whether the efficacy can last for 3 months. To achieve this objective, 72 patients with insomnia will be recruited and randomly assigned to receive taVNS treatment (n =36) or sham taVNS treatment (n = 36) for 8 weeks and 12-weeks followed up. The primary outcome is Pittsburgh Sleep Quality Index (PSQI) score. Secondary and exploratory outcomes include PSQI components, response rate, Insomnia Severity Index (ISI), 17-item Hamilton Depression Scale (HAMD-17), 14-item Hamilton Anxiety Scale (HAMA-14), Epworth Sleepiness Scale (ESS), Flinders Fatigue Scale (FFS) and adverse events. The trial will be conducted in compliance with the protocol, Good Clinical Practice (GCP) and the applicable regulatory requirement(s).

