### 342 343 **Anticipated results**

344 The most expected and scientifically significant findings should be that taVNS treatment may achieved  
345 clinically significant improvements, without aggravating insomnia symptoms and other adverse events,  
346 compared to sham taVNS.

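### No adverse-event assessment is scheduled after week 8, although patients are assessed for efficacy at week 20

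*Protocol*

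**What the plan says.** All the scheduling statements below are in the protocol.

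- **Safety schedule** (Clinical and biochemical assessment, safety paragraph): "Safety assessment will be conducted at 4 weeks, and 8 weeks". No later time point is named.
- **Other assessments** (same section): "Other clinical assessments will be conducted at baseline, 4 weeks, 8 weeks and 20 weeks". Blood pressure is described directly after this sentence. The PSQI components, ISI, HAMD-17, HAMA-14, ESS and FFS are assessed as changes "from baseline to 4, 8 and 20 weeks", and the PSQI total also has a week-20 assessment.
- **Duration** (Treatment procedure): stimulation is given "for 8 weeks, followed by a 12-week observational period".
- **Source of adverse-event data** (Clinical and biochemical assessment): "adverse events (AEs) reported by participants and recorded by physician", and, in the paragraph on secondary outcomes, "Additionally, adverse reactions are recorded". Neither statement has a start or end date.
- **Role of adverse events** (Plan of Investigation): they close the list of secondary and exploratory outcomes, "Epworth Sleepiness Scale (ESS), Flinders Fatigue Scale (FFS) and adverse events".
- **Expected conclusion** (Anticipated results): "clinically significant improvements, without aggravating insomnia symptoms and other adverse events", relative to sham, with no time frame given.

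**The concern.** The trial keeps patients under observation for three months after treatment in order to learn whether the benefit lasts, and it assesses them at the end of that time. The safety schedule does not use that assessment. An event that begins after week 8, or one present at week 8 that does not resolve, reaches the database only if the patient happens to report it.

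Three features of this protocol make that matter:

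- Adverse events are a listed outcome, and the expected conclusion joins benefit and harm without limiting either to a period. As planned, benefit would be assessed systematically over 20 weeks and harm over 8.
- The definition of a serious event includes lasting disability and permanent damage. When the last scheduled enquiry falls at the end of treatment, no planned assessment shows whether an event ongoing then went on or cleared.
- Patients are told that allocation stays unknown until the investigational treatment is complete. The protocol does not say whether it is disclosed at that point. If it is (an assumption), unprompted reports after week 8 could differ between arms because of what patients know.

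**Working it through.** **1. Schedules side by side (Clinical and biochemical assessment)**

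| Domain | Week 4 | Week 8 | Week 20 |
|---|---|---|---|
| PSQI total and components | yes | yes | yes |
| ISI, HAMD-17, HAMA-14, ESS, FFS | yes | yes | yes |
| Other clinical assessments (apparently including blood pressure) | yes | yes | yes |
| Safety assessment | yes | yes | not named |

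No other section of the protocol schedules an adverse-event enquiry between weeks 8 and 20.

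**2. Size of the gap**

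Inputs: 8 weeks of treatment and 12 weeks of observation (Treatment procedure); 72 patients (Plan of Investigation).

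- Time on study: 8 + 12 = 20 weeks, which agrees with the week-20 assessment.
- Share with no scheduled safety assessment: 12 / 20 = 60%.
- In patient-weeks, assuming no dropout: 72 × 12 = 864 of 72 × 20 = 1,440, again 60%.
- Share of the stimulation period covered by the schedule: 8 / 8 = 100%.

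The last two lines belong together. The gap is large in calendar time, but all of it lies after stimulation ends.

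**3. What the week-20 data would and would not show**

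For each adverse event the safety paragraph asks for occurrence, severity, perceived relation to treatment and how it was handled. The week-20 scales yield scores for sleep, mood, anxiety, sleepiness and fatigue. An individual's worsening on one of them would be visible in the data, but the scales supply none of those four fields and do not ask about events outside their own domains.

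**4. Is anything else in the design affected?**

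The sample size rests on PSQI alone. With an SD of 4.3, a difference of 14.9 − 11.1 = 3.8, two-sided α of 0.05 (sidedness assumed) and 90% power, the normal approximation gives 2 × (1.960 + 1.282)² × 4.3² / 3.8² = 26.9, so 27 per arm. Then 27 / 0.75 = 36 per arm, or 72 in total, which matches the stated figure. No safety quantity enters. The primary endpoint is PSQI change at week 8. Adding a safety enquiry at week 20 changes no sample size and no error rate. It extends scheduled coverage from 8 of 20 weeks (40%) to 20 of 20, with no extra visit.

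**The case against.** The strongest defence is that this is a design choice and not a contradiction. Stimulation stops at week 8, so events caused by the device would mostly be expected while it is in use, and that period is fully covered. The three-month aim in Hypothesis and Aims concerns efficacy, and no section promises safety results to week 20. The schedule is the same in both arms, so it does not by itself bias the comparison. All of this stands, and it keeps the point from being a serious one.

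A reader might go further and infer that the trial will have no adverse-event data after week 8, or that later events must be missing from the counts. The documents do not support that. The general statements that adverse events are reported and recorded carry no end date, so spontaneous reports are not excluded. Reasons for withdrawal are recorded whenever a patient leaves before completing the study, and an adverse event is a withdrawal criterion with no limit to the treatment period. What is missing is a scheduled enquiry and a stated collection window.

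A reader might also infer that week 20 is blind to any harm other than poor sleep. That is too strong as well: mood, anxiety, sleepiness and fatigue are scored then, and blood pressure is apparently measured. Nor do the documents name any particular harm expected after the device stops, so the case for the change rests on completeness of ascertainment and not on a known late effect.

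What the defence does not answer is why an existing assessment is left unused. Undated general statements beside an explicit two-visit schedule do not amount to systematic collection; at best they leave the window ambiguous. An analysis plan cannot repair this later, because it cannot tabulate answers to questions that were not asked.

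**Conclusion.** The point holds as a gap in scheduled ascertainment. Safety is assessed at weeks 4 and 8, other domains continue to week 20, and the 12-week observation period (60% of time on study) has no scheduled adverse-event assessment. Events starting or persisting in that period would be captured only through spontaneous reports with no stated window.

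It is minor to moderate. The primary endpoint, the sample size and coverage of the stimulation period are untouched, and no bias between arms follows from the schedule alone. The weight it carries comes from the undated safety conclusion in Anticipated results, which systematic data would support for the first 8 weeks only. The verdict assumes that the safety sentence means what it says, and that the week-20 assessment takes place for patients still in the study.

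**What to change.** In Clinical and biochemical assessment, change the safety schedule to weeks 4, 8 and 20. At the existing week-20 assessment, ask both arms the same questions about adverse and serious adverse events since week 8, and about the outcome of any event ongoing at week 8, using the fields the section already lists. State the collection window. Tabulate events by arm, separately for the treatment period (to week 8) and follow-up (weeks 8 to 20).

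The cost is a few minutes of questions, one case-report page and one more table, with no extra visit. There are two downsides. Some unrelated background events will be recorded, which the separate tabulation keeps apart. A single enquiry also relies on 12-week recall, so milder events will be under-reported and dated loosely. If patients know their allocation by then, a common set of questions reduces the resulting reporting bias but does not remove it.

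If the sponsor prefers not to add the assessment, the protocol should say that scheduled adverse-event collection ends at week 8, and the safety statement in Anticipated results should be limited to the treatment period.

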## **Data analyses**

The analysis will be performed on the intention-to-treat (ITT) population that participants had been randomized. All efficacy analyses will be performed using the ITT analysis set and PP analysis set, defined as all randomized participants who received at least 6-week intervention. A mixed model for repeated measures (MMRM) with likelihood-based modeling to handle missing data will be applied to compare the primary outcome and secondary outcomes: change in the PSQI, ISI, HAMD, HAMA, ESS, FFS scores from baseline to week 4, 8, and 20. The model includes terms for treatment (taVNS or sham taVNS), visit (weeks 4, 8, 20), treatment by visit interaction, and baseline scores. Least squares mean change from baseline and least square mean difference between the groups at week 8 along with 95% confidence interval and a 2-sided p value will be estimated for the primary end point. Cohen d effect size will be calculated using the absolute value of the least square mean difference between groups in score from baseline at week 8 divided by the pooled SD estimated from the mixed model for repeated measures. For the PSQI responder analysis, the responder is defined as a 50% decrease at the end of treatment compared with baseline, which is prespecified in the statistical analysis plan. The percentage of PSQI responder at week 4, 8 and 20 will be calculated and summarized by treatment group. The percentage of PSQI responders at week 8 and 20 will be compared between groups using the Chi-square test. SAS, version 9.4 (SAS Institute Inc) is used for all analyses, with significance set at  $P < 0.05$ .

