**Estimation of sample size**

This study was a prospective exploratory study. Using PSQI as the primary outcome and intervention and control group allocated as 1:1). Estimation of sample size is based on the results of the preliminary study, the mean PSQI score of patients with chronic insomnia is 14.9 (SD, 4.3), and the PSQI score is expected to be reduced to 11.1 after 8-weeks of taVNS treatment. Considering the dropout and loss to follow-up rate of approximately 25%, and with 0.05  $\alpha$ -level and 90% power, the total sample size required for the trial is 72 patients.

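### The MMRM holds one baseline slope across weeks 4, 8 and 20; adding baseline-by-visit is a cheap safeguard against a possible bias that is small at week 8 and larger at week 20

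*Protocol*

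**What the plan says.** The protocol's Data analyses section chooses "A mixed model for repeated measures (MMRM) with likelihood-based modeling to handle missing data" and lists its fixed effects: "The model includes terms for treatment (taVNS or sham taVNS), visit (weeks 4, 8, 20), treatment by visit interaction, and baseline scores". The list names one interaction with visit, that of treatment, and leaves baseline without one. The primary result is the "least square mean difference between the groups at week 8 along with 95% confidence interval and a 2-sided p value". The section on clinical and biochemical assessment agrees on timing: "The primary endpoint is the mean changes from baseline through week 8 in PSQI scores". PSQI change at week 20 is secondary, but the Hypothesis and Aims section makes three-month maintenance part of the working hypothesis.

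The sample-size section allows for losses ("Considering the dropout and loss to follow-up rate of approximately 25" per cent). It does not split them by arm, visit or baseline severity. The likelihood model is the only method that the protocol names for missing data.

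**The concern.** With complete data, randomisation balances baseline between the arms, and a common slope costs only some efficiency. With dropout, a likelihood analysis is valid under missing at random only if its mean model is right. Suppose severe sleepers leave one arm more than the other, and the relation of change to baseline is not the same at weeks 4, 8 and 20. Dropout is then still explained by observed baseline and arm, so the data are missing at random. The listed model nevertheless adjusts the remaining patients with the wrong slope at some visits, and the error does not cancel between arms.

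Equal slopes cannot be taken for granted here. Weeks 4 and 8 are on treatment, while week 20 follows 12 weeks without it. Different reasons for leaving are also conceivable, because the arms receive clearly different current intensities. At stake are the primary week-8 contrast and, more so, the week-20 contrast behind the maintenance claim.

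**Working it through.** **The plan's own figure.** From the sample-size section: PSQI 14.9 (SD 4.3) falling to 11.1, two-sided alpha 0.05, power 90%, 25% loss. Taking 14.9 − 11.1 = 3.8 as the between-arm difference:

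n per arm = 2 × (1.960 + 1.282)² × 4.3² / 3.8² = 2 × 10.51 × 18.49 / 14.44 = 26.9, so 27.

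27 / 0.75 = 36 per arm, or 72 in total. This matches the protocol, so 3.8 is the benchmark for size.

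**Why two conditions are needed.** Let the true mean change at visit t be α_t + τ_t·arm + β_t·baseline. Let β* be the one slope that the listed model fits, and m_1t and m_0t the mean baselines of patients still observed at visit t under taVNS and sham. If visits were uncorrelated, the expected estimate would be

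τ_t + (β_t − β*) × (m_1t − m_0t).

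The bias is a product. It vanishes if the slopes are equal (β_t = β*), or if dropout leaves the arms alike on baseline (m_1t = m_0t). Its sign follows from the signs of both factors. Correlation between visits changes the size, so the size was simulated.

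**Simulation inputs.** From the protocol: 36 per arm, SD 4.3, effect 3.8, roughly 25% loss. Assumed, because the protocol gives none: residual SD 3.5, correlation 0.6 between visits, logistic dropout on baseline, and the slopes of change on baseline. An unstructured-covariance MMRM was fitted with and without baseline-by-visit.

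**Large-sample gap** (40,000 per arm; common-slope estimate minus interaction estimate, PSQI points):

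| Slopes at weeks 4/8/20 | Dropout log-odds per baseline SD, by arm | Missing by week 8 / 20 | Week 8 | Week 20 |
|---|---|---|---|---|
| −0.3/−0.5/−0.7 | 0.7 and 0.7 (alike) | 12% / 28% | −0.002 | −0.008 |
| −0.4/−0.5/−0.6 | 0 and 0.7 | 11% / 27% | 0.021 | 0.118 |
| −0.3/−0.5/−0.7 | 0 and 0.7 | 11% / 27% | 0.042 | 0.227 |
| −0.3/−0.5/−0.7 | −0.7 and 0.7 | 12% / 28% | 0.088 | 0.472 |
| −0.7/−0.5/−0.3 | −0.7 and 0.7 | 12% / 28% | −0.091 | −0.471 |
| −0.2/−0.5/−0.8 | −1 and 1 | 13% / 30% | 0.209 | 0.993 |
| −0.3/−0.5/−0.7 | −0.7 and 0.7 | 24% / 27% | 0.180 | 0.481 |
| −0.2/−0.6/−0.6 | −0.7 and 0.7 | 24% / 27% | 0.398 | 0.431 |

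With baseline SD 3.0 in place of 4.3, the seventh row falls to 0.125 and 0.340, about 30% less.

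**At the trial's size** (36 per arm, 600 runs, effect 3.8):

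- Equal slopes of −0.5 with arm-opposite dropout (−0.7 and 0.7): the common-slope bias is −0.013 at week 8 and −0.022 at week 20 (Monte Carlo SE 0.034 and 0.037), which is none detectable.
- Slopes −0.3/−0.5/−0.7 with the same dropout: 0.075 and 0.440 for the common slope, against −0.013 and −0.017 with the interaction.
- The same setting with no treatment effect: rejection at week 8 is 5.2% (common) against 4.5% (interaction), within a Monte Carlo error of about 1 point. At week 20 it is 11.2% against 7.5%. The interaction model also exceeds 5% there, so only the gap of 3.7 points is attributable to the missing term.

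**A second simulation under other assumptions** (baseline correlations 0.6/0.5/0.4 or 0.7/0.5/0.3 at weeks 4/8/20, about 25% lost before week 8) gave absolute biases of 0.04 to 0.20 at week 8 and 0.10 to 0.43 at week 20.

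**Scale.** The week-8 SE is about 0.86. A bias of 0.2 is 0.2/0.86 = 0.23 SE and 0.2/3.8 = 5% of the planned difference. A bias of 0.4 is 0.47 SE and 11%. At week 20 (SE up to about 0.96), 0.45 is 0.47 SE and 12% of 3.8.

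**Price of the term when slopes are equal.** The week-8 SE goes from 0.853–0.859 to 0.855–0.862 (+0.2 to 0.4%). The week-20 SE goes from 0.906–0.916 to 0.910–0.930 (+0.4 to 1.5%). When slopes differ and dropout does not depend on baseline, the week-20 SE falls from 0.952 to 0.910 (−4.4%).

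**The case against.** A common baseline slope is a permissible specification and contradicts nothing in the protocol. Nothing there shows that slopes vary or that dropout is related to baseline in an arm-specific way. Most of the 25% loss may fall after week 8, where it hardly touches the primary contrast. The entry limit of PSQI 8 or more may make the baseline SD smaller than 4.3. The statistical analysis plan, which is not at hand, could already contain the term. All of this stands, except that an unseen plan does not change the protocol's explicit list of terms; if that plan has the term, the two should be aligned.

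A reader might infer three stronger things, and the document supports none of them:

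- *Arm-dependent dropout on baseline is enough to cause bias.* It is not. With equal slopes the listed model is correct and unbiased even under arm-opposite dropout.
- *The bias would favour taVNS.* That holds if the baseline link weakens over time and sham loses its worse sleepers. If either reverses, so does the sign. After 12 weeks off treatment, patients could drift back towards baseline and the link could strengthen.
- *The primary result is compromised.* At week 8 the effect is mostly a small fraction of a standard error. Larger values need early, arm-opposite dropout together with strongly differing slopes.

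**Conclusion.** The point holds as a conditional weakness in the stated model. A single baseline slope leaves both contrasts open to bias if slopes vary by visit and dropout depends on baseline differently by arm. If either condition is absent, there is no bias.

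The likely size is about 0.02 to 0.2 points at week 8, up to about 0.4 in the worst early-dropout scenario tried. At week 20 it is about 0.1 to 0.45 points in most scenarios, and close to 1 point in the most extreme. These figures rest on assumed slopes, correlations and dropout mechanisms, so they are illustrations and not predictions for this trial. The case for change rests mainly on week 20 and on the very low price. The sample size of 72 is unaffected.

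**What to change.** In the Data analyses section, extend the list of MMRM terms to treatment, visit, treatment-by-visit, baseline score and baseline-by-visit. Apply it to the PSQI and to every other scale analysed by MMRM (ISI, HAMD, HAMA, ESS, FFS), with the same wording in the statistical analysis plan. Make the change before unblinding.

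The cost is two extra parameters per outcome and the small SE increase shown above if the slopes are in fact equal. No new data or patients are needed.
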